A routine CAD screening induces high healthcare expenses as it leads to invasive investigations, endovascular and surgical revascularizations as well as intensification of pharmacological therapies. To the best of our knowledge, the cost-effectiveness of routine CAD screening has not been evaluated prospectively in population with T2DM and a very high cardiovascular risk. Only two economic studies, based on Markov models, have addressed this question by comparing different strategies in Japanese and American populations: no screening, screening (with stress echocardiography, myocardial scintigraphy coupled with stress test, or stress electrocardiogram) [21, 22]. Their results were very limited by model’s hypothesis; uncertainty surrounding epidemiological and utilities data used; and costs of care, which may differ greatly across countries. In this context of discrepancy between lack of evidence and current guidelines and clinical practice, we aim to estimate the effectiveness and cost-effectiveness of systematic CAD screening in patients with T2DM and a very high cardiovascular risk.

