### Recruitment of participants and follow‑up

The data will be extracted from January 1, 2008 to December 31, 2019. A selection period will be defined by the 7 years (January 1, 2008 to December 31, 2014) preceding the index date. It will enable us to identify eligible patients and measure all the variables needed for the calculation of the high dimension propensity score (hdPS). Each participant will be assigned to one of the two study groups on the index date (January 1, 2015), and then followed up to December 31, 2019 (Fig. 1).

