### Study groups and methods of CAD screening

#### Screening group

Individuals who had at least one screening exam (stress electrocardiogram test, stress echocardiography, myocardial scintigraphy coupled with stress test or pharmacological stimulation using adenosine, or coronary CT scan) (Table 2) during the selection period (2008–2015).

**Table 2 Tab2:** Codes used to identify tests to screen coronary artery disease

Tests	Procedure codes
Stress test	DKRP004, EQRP002, EQRM001
Myocardial scintigraphy coupled with stress test or pharmacological stimulation using adenosine	DAQL001, DAQL010, DAQL011, DAQL009
Stress echocardiography	DAQM003, DZQM002, DBQM001
Coronary CT scan	ECQH010
Procedure codes: Codes of the French classification of medical procedure (CCAM)	

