### Study endpoints

#### Primary endpoint

The incremental cost per life year saved over 5 years in CAD screening group *versus* no CAD screening.

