### Secondary endpoints

#### Economic endpoints

(1) A cost-consequence analysis linking the total 5-year direct costs of each strategy (drugs, medical visits, hospitalizations, nursing visits, biological and radiological exams, technical exams, medical transports…) and the total number of major cardiovascular and renal events over 5 years; (2) the budget impact (in €) for the French Insurance system to promote the most cost-effective strategy between routine CAD screening and no screening; and (3) the total care consumption over the follow-up period.

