### Statistical analysis plan

The data will be analysed by the biostatistician of the “Clinical Epidemiology Unit” of the University Hospital of Bordeaux (USMR). Analyses will be performed using SAS® software, version 9.4 or later (SAS Institute, Cary, NC, USA, http://www.sas.com) and all tests will be performed at the first-order error risk α = 5%. The flow-chart (CONSORT), as well as the characteristics of patients at inclusion (eligibility criteria, epidemiological, clinical, biological characteristics and treatment use) will be presented. Confounding factors will be taken into account through a hdPS score that will involve around 500 variables, according to the Bross formula [26]. A principal component analysis will then allow us to reduce the dimensionality to 30 components, and the goodness of fit of this hdPS score will be estimated by a graphical comparison of the score distribution and by standardized mean differences between the two study groups [27]. Comparisons between the two groups will be carried out with and without adjustment for the hdPS score, and the hypotheses of the different regression models chosen, will be systematically verified.

Regarding the analysis of the primary endpoint, a gross estimate of the incremental cost per life-year gained at 5 years will be conducted. The confidence interval (CI) of this incremental cost-effectiveness ratio will be estimated by boostrap (5000 iterations). The analysis will be performed as Intent to Treat. To investigate a possible relationship between the frequency of screening and survival, we will define four different subgroups: screening conducted at least once a year, less than once a year (and at least once every two years), less than once every two years (and at least once every three years), and only once during the follow-up period.

A cost-consequence analysis will be performed linking results of all direct costs (observed during the following period) and results on major cardiovascular events. A budget impact analysis will be conducted to determine the public expenses of the spread of a systematic screening for silent ischemic CAD.

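### The 5-year cost window opens after the exam that defines the screening group, so that exam and its pre-2015 work-up fall outside the primary ICER

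*Protocol article*

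**What the plan says.** All references are to the protocol article.

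- **Recruitment of participants and follow-up:** "A selection period will be defined by the 7 years (January 1, 2008 to December 31, 2014) preceding the index date". Then "Each participant will be assigned to one of the two study groups on the index date (January 1, 2015", and each participant is "followed up to December 31, 2019". The section gives the selection period two uses: finding eligible patients and measuring the variables for the high-dimension propensity score (hdPS). Costing is not among them.
- **Screening group:** "Individuals who had at least one screening exam" in the selection period. This section and the one on the no-screening group label the period 2008-2015, whereas the recruitment section ends it on 31 December 2014.
- **Primary endpoint:** "The incremental cost per life year saved over 5 years in CAD screening group", compared with no screening. The statistical analysis plan section likewise estimates it at 5 years.
- **Economic endpoints:** a cost-consequence analysis "linking the total 5-year direct costs of each strategy" to event counts. The statistical analysis plan section describes the cost side as "linking results of all direct costs (observed during the following period", which I read as the follow-up period.
- **Background:** "A routine CAD screening induces high healthcare expenses as it leads to invasive investigations, endovascular and surgical revascularizations".

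**The concern.** A cost-effectiveness ratio should charge each strategy with what it costs to deliver and with what it sets in motion. Here, delivery of the strategy is what places a patient in the screening arm, and it is complete before cost counting begins. The early consequences of an exam (invasive tests, admissions, procedures, treatment changes) come soon after it, so for most of the selection period they too would fall before 2015. These are the expenses that the Background gives as the reason for the study.

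Controls by definition had no screening exam in the selection period, so the missing exam cost belongs to one arm only. Neither hdPS adjustment nor the bootstrap can restore a cost that was never counted. The primary endpoint and the cost-consequence analysis would then describe spending after 2015 among people already screened, and the cost of screening them would be absent.

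**Working it through.** The plan gives no unit cost, life-year gain or ICER, so there is no figure of its own to reproduce on this point. The check is on dates, followed by a labelled illustration.

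**1. The windows**
- Exposure: 1 January 2008 to 31 December 2014 = 7.0 years.
- Follow-up: 1 January 2015 to 31 December 2019 = 5.0 years.
- Overlap: 0 days.

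The 2008-2015 label does not change this, because assignment takes place on 1 January 2015 and so the defining exam still precedes follow-up.

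**2. Exams counted**
- Screened once, before the index date: 0 of 1 exams costed.
- Screened yearly throughout: 7 uncounted, 5 counted.
- Any constant rate over the 12 years: 7 / (7 + 5) = 58% uncounted.

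**3. Effect on the ratio**

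Let ΔC be the incremental cost counted in 2015-2019, P the omitted pre-index incremental cost per screened patient, and ΔLY the incremental life-years.

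- ICER as planned = ΔC / ΔLY
- ICER with pre-index costs = (ΔC + P) / ΔLY
- Shift = P / ΔLY

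Incremental cost is understated by P whatever ΔLY is. The shift in the ratio is interpretable only if ΔLY is positive.

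**4. Illustration (none of these inputs is in the document)**

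For P from EUR 100 to EUR 1,000 and ΔLY from 0.02 to 0.10:
- smallest shift: 100 / 0.10 = EUR 1,000 per life-year
- largest shift: 1,000 / 0.02 = EUR 50,000 per life-year

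To see which ΔLY might arise, take 5-year restricted mean survival as (1 − exp(−5h)) / h with assumed control mortality h = 0.05 per year:
- hazard ratio 0.90 (h = 0.045): gain 0.0534 years; each EUR 100 omitted moves the ICER by 100 / 0.0534 ≈ EUR 1,900
- hazard ratio 0.95 (h = 0.0475): gain 0.0266 years; each EUR 100 omitted moves it by 100 / 0.0266 ≈ EUR 3,800

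A 5-year life-year gain is small under any such assumption, so modest omitted costs can move the ratio a long way. The figures show this sensitivity and do not estimate the bias.

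**5. The CAD exclusion**

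The exclusion criteria remove people with a history of acute coronary syndrome, coronary revascularization or angina, without saying at what date the history is read. If it is read up to the index date, patients whose exam led to such a diagnosis or procedure before 2015 leave the cohort, taking both their costs and their life-years with them.

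**The case against.** The strongest reply has five parts.

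- **The explicit cost window belongs to a secondary analysis.** The sentence on costs observed in follow-up concerns the cost-consequence analysis, and for the primary ICER the text says only 5 years. This is correct. But the document contains one 5-year window and gives the selection period no costing role, so 2015-2019 is the natural reading for the ICER too. Detailed costing rules may sit in the full protocol; the window itself is fixed here.
- **Screening costs are not absent.** A reader might infer that the ICER leaves out the cost of the intervention altogether. The document does not support that. Repeat exams, work-up after 1 January 2015 and continuing drug costs are counted, and the Background survey suggests repeat screening is common. What is missing is the pre-index exams and their pre-index consequences.
- **The budget impact may be unaffected.** A reader might extend the bias to it, but the document states no cost inputs or window for that analysis.
- **Post-index exams in controls are charged to controls.** This narrows the cost gap, but it is what the stated intention-to-treat approach does and is not a separate error.
- **The exclusion of screen-detected CAD is not established.** It depends on an assessment date that the text does not give. It would also remove life-years, so its net effect on the ICER cannot be called favourable to screening.

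The first part stands as a point about where the text is explicit. The other four limit the scope. None of them brings the defining exam into the numerator.

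**Conclusion.** The point holds for the primary ICER, where the window is inferred from the only stated follow-up, and for the cost-consequence analysis, where it is explicit. The defining exam and its work-up before 2015 are not costed. Omitting them lowers incremental cost and so favours screening. The share of exams affected ranges from all of them (one exam, before the index date) to 58% under constant screening over 12 years.

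The size in euros cannot be derived from the document, and the illustration above rests wholly on assumed costs, mortality and hazard ratios. It also needs a positive life-year gain, whereas all four hazard ratios in Table 1 have intervals that include 1.

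The stronger readings, that no screening cost is counted, that the budget impact is biased, or that patients revascularized after screening are certainly excluded, go beyond what the document says.

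**What to change.** 1. **Keep 1 January 2015 as the index date.** Add to the ICER and cost-consequence numerators all direct costs from first exam to 31 December 2014, with a matched calendar date in controls. Everyone in the cohort is alive on 1 January 2015, so life-years over that earlier interval do not differ between the arms and the denominator needs no matching change. Taking all direct costs, not the exam alone, also credits screening with any savings before 2015.
2. **Report the ICER with and without these costs,** and state the cost window for the primary analysis in words.
3. **Fix the date at which the CAD exclusion is assessed,** and limit the conclusion to patients alive and free of CAD at the index date.
4. **Reconcile the text:** the end of the selection period (31 December 2014 or 2015), and the frequency subgroup defined by screening only once in follow-up when exposure is defined before it.

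Two alternatives should be avoided. Restarting the clock at the exam date in the cohort assigned in 2015 creates immortal time, because a patient examined in 2010 must survive to 2015 to be included, and controls are chosen by having no exam over the whole period. Exam-date time zero would need a cohort rebuilt with eligibility assessed at that date. Adding back the costs of excluded patients without their life-years would load the numerator against screening.

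The cost is some programming and protocol wording; the 2008-2014 claims are already in the extraction. The ICER may look less favourable to screening.

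### The primary ICER is fixed only as a gross estimate; nothing states that its cost difference is adjusted, by the hdPS or for cost before the exam

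*Protocol article*

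**What the plan says.** The primary endpoint is incremental cost per life-year saved over 5 years, screening versus no screening. The Statistical analysis plan section gives two sentences on estimating it: "a gross estimate of the incremental cost per life-year gained at 5 years will be conducted", and "The confidence interval (CI) of this incremental cost-effectiveness ratio will be estimated by boostrap (5000 iterations"). No cost model and no cost covariate is named there.

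The cost window is follow-up. Economic endpoints refers to "the total 5-year direct costs of each strategy", and the Statistical analysis plan section describes the cost-consequence analysis as "linking results of all direct costs (observed during the following period").

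On confounding, the same section is general: "Confounding factors will be taken into account through a hdPS score that will involve around 500 variables", and "Comparisons between the two groups will be carried out with and without adjustment for the hdPS score". The Abstract likewise says that analyses will be adjusted for the score and makes no exception for cost. The only model explicitly tied to the score is the Cox model for clinical events.

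On available data, Recruitment of participants and follow-up states: "The data will be extracted from January 1, 2008 to December 31, 2019". The years 2008 to 2014 form the selection period, used to establish eligibility and to measure the hdPS variables. The exam that puts a patient in the screening group may fall anywhere in that period.

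**The concern.** Cost is the numerator of the primary ratio. It covers drugs, visits, hospital stays, nursing, transport and examinations, in people with diabetes for at least 7 years and established vascular disease. Much of this is chronic care, so earlier cost is likely to be a strong predictor of later cost. Heavier users of care also have more occasions to be sent for a test. Strengths and limitations itself concedes selection bias and confounding.

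If the headline ratio is the gross one, any cost difference between the groups that preceded the exam passes into the incremental cost and is read as an effect of screening. The bootstrap describes sampling variation around that figure and does not correct it; nor does a cohort of 90,000. Because the ratio divides by a life-year difference that may be small, a modest bias in cost can move it a long way.

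The hdPS may remove part of this, but the article does not say that the primary ratio relies on it. The score is also not built to target cost: the Bross formula ranks covariates by their association with exposure and with a binary outcome, and the selected variables are then reduced to 30 components.

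**Working it through.** **1. The sentences side by side.** Specific to the primary ratio: a gross estimate with a bootstrap interval. General: all group comparisons with and without the hdPS. Both can be carried out, but the article does not say which gives the main result, or whether the bootstrap includes the adjustment. Prior cost is neither named in nor excluded from the roughly 500 variables.

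**2. The one stated figure nearby.** Sample size estimation: 2,400,000 × 0.38 × 0.10 = 91,200, consistent with at least 90,000 eligible patients. This is a feasibility count. The article gives no cost standard deviation, baseline cost gap or correlation between earlier and later cost, so steps 3 to 5 rest on assumed ranges.

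**3. Possible bias in the cost difference, before any hdPS adjustment.** Bias = 5 years × annual gap × persistence.

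| Gap (euro/year, assumed) | Persistence 0.3 | 0.5 | 0.7 |
|---|---|---|---|
| 100 | 150 | 250 | 350 |
| 300 | 450 | 750 | 1,050 |
| 500 | 750 | 1,250 | 1,750 |

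The sign follows the direction of the gap, which is unknown.

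**4. Effect on the ratio, for scale only.** Life-years over 5 years at constant hazard h are (1 − exp(−5h))/h. At h = 0.05 this is 4.424; at h = 0.045 (10% lower mortality) it is 4.477; the difference is 0.053. Taking 0.05 life-years, 150 euro shifts the ratio by 150/0.05 = 3,000 euro per life-year, 750 euro by 15,000 and 1,750 euro by 35,000. The mortality rate and the benefit are both assumed.

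**5. Precision.** Adjusting for prior cost with correlation r multiplies the standard error of the cost difference by √(1 − r²): 0.95 at r = 0.3, 0.87 at 0.5, 0.71 at 0.7. This applies to the cost difference without the hdPS, not directly to the interval of the ratio.

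**6. How much pre-exam history exists.** Extraction starts in 2008.
- One exam at a uniformly random time in the 7 years: mean history 3.5 years; 1/7 = 14% have under 12 months.
- Regular screening at the frequencies in the physician survey in Background (42% yearly, 20% two-yearly, 33% three-yearly), first captured exam uniform within the interval: mean (0.42 × 0.5 + 0.20 × 1 + 0.33 × 1.5)/0.95 = 0.95 year; share under 12 months (42 + 20/2 + 33/3)/95 = 63/95 = 66%.

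The second case applies what physicians report to individual patients, so it is a rough bound. It shows that short history may be common.

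**The case against.** The strongest reply is that the plan does promise hdPS-adjusted comparisons, in the Abstract and in the Statistical analysis plan section, with a score drawn from the same 2008 to 2014 claims. The variable list is not in the article and may sit in the full protocol, so prior cost or markers of earlier care use may already be included. This stands. A reader might infer that the incremental cost is left wholly unadjusted; the documents do not support that. The absence of the list is no finding either.

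Three further points also stand. Counting outcome costs only in follow-up is not an error, and the sentence that does so defines the window of a secondary analysis. Calling prior cost the strongest predictor would go beyond the documents, which give no cost correlations. Nor can one assume years of pre-exam claims for every patient: early and regular screeners have little, exams before 2008 are not seen, and controls have no exam date.

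It can also be said that every figure in steps 3 to 5 is assumed, and that what matters is the bias remaining after the hdPS. That is correct, and the figures show scale only. It does not remove the ambiguity: the one estimator stated for the primary endpoint is the gross one.

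**Conclusion.** The point holds in a limited form. The primary ratio is specified only as a gross estimate beside a general promise of adjusted comparisons, and nothing states that its cost difference is adjusted for earlier cost. In a non-randomised comparison, a cost gap that preceded screening could therefore be attributed to it. The size is unknown from the documents: 150 to 1,750 euro per patient under the assumed gaps and persistence before any hdPS adjustment, and less to the extent that the score captures earlier care use. Any gain in precision is secondary. This does not invalidate the study, but it bears on the primary endpoint and should be settled before analysis.

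**What to change.** - Make the hdPS-adjusted ICER the main estimate. Re-estimate the adjusted cost difference and the adjusted life-year difference in each of the 5000 bootstrap iterations. Keep the gross ICER as supportive.
- Add annualised direct cost before the first captured exam as a covariate in the cost model for the ICER and for the cost-consequence analysis. In the no-screening group, measure it before an assigned, matched calendar date. Cost over the whole pre-index period should not be used, because it contains the exam and its consequences, and adjusting for it could remove part of the strategy's own cost.
- Report this prior cost by group as a balance item.
- Use whatever pre-exam time is available, with an indicator for short history. As a sensitivity analysis, restrict to patients with at least 12 months of pre-exam data.

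The extraction window already covers the claims needed, so the cost is analysis work plus the assignment of reference dates to controls. The remaining weaknesses are thin baseline data for early or regular screeners and pre-exam cost that may include the consequences of an unseen exam before 2008. Both should be stated with the results.

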### Study population

#### Inclusion criteria

Eligible participants must meet all of the following criteria:Age = 40 years or older,Affiliation to the general health insurance scheme in France,Diagnosis of T2DM,Duration of T2DM ≥ 7 years,Two or more additional cardiovascular risk factors (obesity, hypertension, hypercholesterolemia, or tobacco smoking using the chronic obstructive pulmonary disease (COPD) as a proxy),At least one microvascular or macrovascular disease: carotid stenosis, transient ischemic attack (TIA), stroke, lower-limb peripheral artery disease (PAD), CKD, severe diabetic retinopathy with requirement of laser photocoagulation, or peripheral or autonomic diabetic neuropathy.

Diagnosis will be determined based on the list of 100% health insurance coverage for chronic diseases in France (including T2DM, hypertension, TIA, stroke, PAD, CKD, COPD), the history of diseases of interest or surgery (coronary, carotid or lower-limb revascularization, bariatric surgery, kidney transplantation) according to the International Classification of Diseases Code Tenth Revision (ICD-10) (Additional file 1: Table S1), or at least 3 deliveries of one or more corresponding drugs as appropriate (antidiabetic, anti-obesity, antihypertensive or lipid-lowering drugs) over one year.

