#### Clinical endpoints

The effects of CAD screening (versus no CAD screening) in terms of major adverse cardiac events (the first occurrence of any component of the composite outcome, which comprise acute coronary syndrome, coronary revascularization, hospitalization for heart failure or all-cause death); major cerebrovascular events (the first occurrence either of stroke, hospitalization for TIA, or carotid revascularization); major adverse limb events (the first occurrence of any component of the composite outcome, comprising PAD, ischemic diabetic foot, lower-limb revascularization (angioplasty or surgery) or amputation); and CKD or end-stage kidney disease (ESKD, defined as requirement of any sustained renal replacement therapy or kidney transplantation). Each component of these composite endpoints will also be considered individually. Major cerebrovascular events, major adverse limb events and ESKD will be considered during follow-up among participants without a history of each appropriate condition at baseline. Clinical endpoints will be determined according to ICD-10 and codes of the French classification of medical procedure (CCAM) as presented in Additional file 2: Table S2.

Finally, SCADIAB study will also assess the frequency of routine CAD screening, expressed as the number of examinations performed per individual per year.

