Cardiovascular events will be expressed as numbers, cumulative incidence and incidence rates. Kaplan–Meier curves will be elaborated to plot the incidence of endpoints according to study groups (CAD screening versus no screening). Unadjusted comparisons between groups will be done using a log-rank test. Cox proportional hazards regression models will be computed to estimate Hazard ratios, with related 95% CIs, after adjustment for hdPS score.

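### Secondary clinical endpoints: the no-history rule leaves prevalent CKD at risk for the renal endpoint, and Kaplan-Meier curves overstate absolute risk for endpoints that exclude death

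*Protocol article*

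**What the plan says.** **Renal endpoint.** In the protocol article, Clinical endpoints closes its list of outcomes with "and CKD or end-stage kidney disease", where ESKD means sustained renal replacement therapy or a kidney transplant. A later sentence in that section sets the baseline restriction: "Major cerebrovascular events, major adverse limb events and ESKD will be considered during follow-up among participants without a history" of the condition in question. CKD is not in that sentence. Inclusion criteria names CKD among the micro- or macrovascular diseases that make a patient eligible: "lower-limb peripheral artery disease (PAD), CKD, severe diabetic retinopathy with requirement of laser photocoagulation".

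**Incidence estimation.** Under Statistical analysis plan, events are to be reported as counts, as cumulative incidence and as rates. For the graphical display, Kaplan-Meier "curves will be elaborated to plot the incidence of endpoints according to study groups". Then, "Unadjusted comparisons between groups will be done using a log-rank test", and "Cox proportional hazards regression models will be computed to estimate Hazard ratios, with related 95% CIs, after adjustment for hdPS score". According to Clinical endpoints, all-cause death is part of the cardiac composite only. The cerebrovascular, limb and renal endpoints leave it out. Every component is also to be analysed alone, which adds acute coronary syndrome, heart-failure hospitalization and coronary revascularization as endpoints without death. Competing risks are not mentioned.

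**The concern.** These are two separate problems.

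1. *Prevalent CKD.* For the other non-cardiac endpoints, the plan removes patients who already have the condition. For the renal endpoint it removes only those with ESKD. A patient who entered because of CKD therefore remains in the risk set of an endpoint that CKD itself satisfies. The renal result would then mix new disease with existing disease coded again. Economic endpoints links costs to a 5-year total that includes renal events, so re-coded cases could enter that total. They could also enter the renal Cox comparison.

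2. *Death as censoring.* A patient who has died cannot later have a stroke, an amputation or a heart-failure admission. If deaths are censored, one minus Kaplan-Meier (1−KM) estimates the risk as though these patients could still have the event. That is higher than the risk patients actually face. If mortality differs between the screened and unscreened groups, the overstatement differs too. The primary endpoint is cost per life year saved, so a mortality difference is what the study sets out to measure.

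**Working it through.** **The plan's own figure.** The only size given is the number eligible: 2.4 million × 0.38 × 0.10 = 91,200, which agrees with at least 90,000. The article gives no mortality, no event rate for these endpoints and no share with CKD at entry. All rates below are assumptions, shown as ranges.

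**Prevalent CKD.** Let p be the share with CKD but no ESKD at baseline, r the share of these re-coded as an endpoint during follow-up, and C the 5-year incidence in those free of CKD.

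Observed proportion = p·r + (1 − p)·C

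C is calculated with death competing at 5% per year, and event rate λ of 2% or 4% per year:

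- λ = 2%: 0.02/0.07 × (1 − exp(−0.35)) = 8.4%
- λ = 4%: 0.04/0.09 × (1 − exp(−0.45)) = 16.1%

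| p | r | C | Observed | Ratio to C |
|---|---|---|---|---|
| 20% | 50% | 16.1% | 22.9% | 1.4 |
| 20% | 50% | 8.4% | 16.8% | 2.0 |
| 35% | 50% | 8.4% | 23.0% | 2.7 |
| 35% | 90% | 16.1% | 42.0% | 2.6 |
| 50% | 90% | 8.4% | 49.2% | 5.8 |

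The ratio over the full grid runs from 1.4 to 5.8. The second and third rows show the effect on a group contrast. If one group has 20% and the other 35% with CKD at entry, with the same new-onset incidence of 8.4% and half of the prevalent cases re-coded, the crude figures are 16.8% and 23.0%. That is a gap of 6.2 points with no difference in new disease. Adjustment for the high-dimensional propensity score (hdPS) may remove part of such an imbalance, but it does not turn a re-coded case into a new one.

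**Kaplan-Meier.** With constant event hazard λ, death hazard μ and T = 5 years:

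- 1−KM with deaths censored = 1 − exp(−λT)
- Cumulative incidence with death competing = λ/(λ + μ) × (1 − exp(−(λ + μ)T))

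For λ = 2% per year, 1−KM is 1 − exp(−0.10) = 9.5% whatever the mortality:

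| Mortality per year | Cumulative incidence | Relative excess of 1−KM |
|---|---|---|
| 2% | 9.1% | 5% |
| 4% | 8.6% | 10% |
| 6% | 8.2% | 15–16% |
| 8% | 7.9% | 21% |
| 10% | 7.5% | 26–27% |

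The relative excess hardly changes for event rates of 1% or 4% per year. As one more case, 3% events and 5% deaths per year give 13.9% against 12.4%.

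With the same event hazard of 2% in both groups and mortality of 4% in one and 6% in the other, Kaplan-Meier shows 9.5% in both. The actual risks are 8.6% and 8.2%.

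**The case against.** **On CKD.** The restriction sentence shows that incident events are intended, and ESKD may be shorthand there for the whole renal endpoint. Endpoint codes are in Additional file 2: Table S2, which is not shown, so whether a routine CKD claim counts as an event cannot be settled from the article. Both remarks stand. They limit what can be said about size, but the written rule still leaves prevalent CKD at risk. A reader might infer that every patient who qualifies through CKD is free of ESKD and will be counted at the next claim. The documents support neither step: Inclusion criteria sets no upper stage for CKD and uses kidney transplantation as a diagnostic history, and the claim rule depends on the missing table.

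**On Kaplan-Meier.** The article never states that deaths are censored, and it lists cumulative incidence separately from the curves. All participants share one index date and one end date, in a database that includes the death registry. With little loss to follow-up, the simple proportion with an event by 5 years would already be the correct cumulative incidence. Competing-risk details are also often left to a full analysis plan. This narrows the point to the curves and any figure read from them. It does not remove it, because the article names Kaplan-Meier as the method for showing incidence, and censoring at death is the usual way to apply it to an endpoint without death.

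Two stronger readings are tempting:

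- *That overstated Kaplan-Meier incidences feed the cost-consequence and budget-impact results.* Economic endpoints links costs to event totals, and nothing in the article passes the curves to either analysis.
- *That every incidence measure and hazard ratio is inflated.* Counts and person-time rates are not inflated by censoring at death, and a Cox model that censors deaths validly estimates a cause-specific hazard ratio.

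**Conclusion.** Both points hold for the secondary clinical endpoints. The primary endpoint, cost per life year saved, is not affected.

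- *Prevalent CKD* is the potentially larger problem. The gap is in the wording. Its size depends on CKD prevalence at entry and on the endpoint codes, neither of which is shown. The range of 1.4 to 5.8 times new-onset incidence rests on 20–50% prevalence, 50–90% re-coding, 2–4% new-onset events and 5% deaths per year. It can affect the renal Cox comparison and the renal part of the cost-consequence event total. The article does not say whether the no-history rule applies to that total, and Statistical analysis plan mentions only cardiovascular events when it describes the same analysis.
- *Kaplan-Meier* overstates absolute 5-year risk for endpoints that exclude all-cause death. If deaths are censored, the direction is certain. The size is about 5% to 26–27% relative over assumed mortality of 2–10% per year, and it differs by group if mortality does. The cardiac composite and all-cause death itself are not affected.

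**What to change.** 1. Restrict the CKD component to participants without CKD at baseline, and analyse ESKD separately in all participants without ESKD at baseline. State whether the renal total in the cost-consequence analysis counts new-onset events under the same rule. The cost is fewer patients in the CKD analysis.
2. For every endpoint that excludes all-cause death, plot and report Aalen-Johansen cumulative incidence with death as a competing event, in place of 1−KM. Keep Kaplan-Meier for the cardiac composite and for all-cause death. Weighting the curves by the hdPS is optional, since the article specifies adjustment rather than weighting.
3. Keep the Cox models, and interpret their estimates for these endpoints as cause-specific hazard ratios. The log-rank test compares the same cause-specific hazards, so it may not match the contrast between the new curves. A sentence should say so.

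All three are changes of wording carried out with standard SAS procedures. No new data are needed.
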